### Recruitment

Recruitment started in the end of October 2023 via online advertisements, flyers, and a study website. A total of 70 participants will be recruited until recruitment is complete. Interested individuals can register on the study website and participate in a screening survey. Participants who are deemed eligible by study staff will be informed of their eligibility and receive the informed consent document. The document contains detailed information about the intervention, study procedures, potential risks and benefits of study participation, data handling and data protection. Consent can be given online by clicking on a “I consent” checkmark box. Upon submitting their informed consent form (Appendix B) electronically, participants will be emailed an electronic link to the baseline survey (t_0_). To prevent individuals from participating in the survey more than once, study staff will screen for duplicates of first and last names and email addresses during registration.

### Incentives

Participants will receive 10€ for each completed survey (t_1_- t_4_). For participation in the semi-structured interviews, participants can earn another 10€ for each interview for a total incentive of 60€ once the study has ended.

### Participant timeline

The study will be conducted over a six-month period, during which a total of five surveys will be administered and two interviews will be conducted with a subgroup of participants. Quantitative data collection will take place at t_0_, 4 weeks post-baseline (t_1_), 8 weeks post-baseline (t_2_), 12 weeks post-baseline (t_3_) and 24 weeks post-baseline (t_4_). All participants will receive access to the nuumi intervention directly after t_0_ data collection. Participants will be granted 2 weeks to complete each survey. Primary and secondary outcomes of this study will be answered by analyzing t_3_ and t_4_ data. To minimize fraud potential, survey invitations are personalized and can only be accessed with an individual access key. Surveys can only be completed once by using the individual access key.

Semi-structured interviews will be conducted by research staff with a sub-sample of 15 enrolled participants via videocall or telephone at t_0_ and t_3_. Participants are invited to partake in the baseline survey. Interested participants will indicate their willingness to be invited via email at the end of the baseline survey and will be sent an informed consent form to be signed electronically (Appendix B). The first interview will be conducted within 2 weeks after t_0_, and the second interview within 2 weeks after t_3_. In interview 1, participants will be asked about previous cessation attempts and perceived barriers to smoking cessation, their perceptions, and attitudes towards ECs and towards the use of smartphone apps for smoking cessation. In interview 2, participants will be interviewed about their current smoking and EC use status, their perceptions of the different intervention features, and the perceived effectiveness of the program. Participants may participate in both interviews, however, having participated in the first interview is not a prerequisite for participation in interview 2.

Participant flow and study design are outlined in Fig. 1 in an adapted Consolidated Standards for Reporting Trials (CONSORT-EHEALTH) diagram for pilot and feasibility trials [52, 53].

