### Objectives

The primary objective of this study is to assess initial efficacy of the nuumi program, defined as self-reported 7-day point prevalence abstinence from smoking at 12 weeks and 24 weeks after initiation. Secondary objectives are to examine within-group changes in smoking cessation-related and psychological outcomes, including urges to smoke, perceived stress, mindfulness, self-efficacy to abstain from smoking, subjective health, and life satisfaction. A further secondary objective is to investigate the acceptability of the nuumi program, indexed by perceived usefulness in quitting smoking, user satisfaction, comprehensibility of the content, and usability of the app. The objective of the qualitative interviews is to explore the perspectives of adults who smoke on quitting using electronic cigarettes and apps before the intervention, and their perspective about the intervention after completion. Overall objective of this single-arm trial is to pilot and optimize procedures of a subsequent RCT, in which the nuumi intervention will be compared to a treatment-as-usual (TAU) control group.

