### Intervention

Nuumi is a self-guided digital therapeutic intervention comprising an app-based behavioral therapy and an EC connected to the app via Bluetooth. Initially, participants are asked to use the EC whenever they crave a cigarette, hence replacing cigarettes with the EC. In parallel, participants are prompted to use the app-based behavioral therapy providing information on transitioning to the EC, and smoking cessation. The app also contains information on gradual EC cessation, thus supporting the user in achieving abstinence of both products.

After completion of the baseline survey, participants receive instructions to download the app and will receive a voucher allowing them to order the EC and pods lasting for a minimum of 3 months from the manufacturer’s website at no cost. Participants are also issued a prepaid return label to return unused pods to the manufacturer in case they decide to stop using the EC and/or the program altogether.

Participants are not required to quit smoking immediately after baseline; they are advised to switch from combustible cigarettes to using the EC either by choosing a quit date, or by gradually switching from smoking to using EC over a 2-week period. The EC has been developed and manufactured by the funder of this study. It is a closed system device; i.e. empty pods cannot be refilled by the user and must instead be replaced with prefilled pods obtained through the manufacturer which can only be used after activation via the app.

Participants will receive a kit including the EC, a charger, a power bank, pods, and manuals for the EC and the pods via mail. Each participant will be supplied with an amount of pods equivalent to their respective cigarette consumption at study entry, estimated according to a guideline by the manufacturer. Participants can choose between two kinds of tobacco flavors when ordering the EC. The liquid solution in the pods includes propylene glycol, glycerol, nicotine, and flavoring. The EC is puff activated and the settings cannot be modified by the user. It is powered by a 450 mAh battery.

The participants receive pods in nicotine strength 20 mg/ml to 0 mg/ml, decreasing in steps of two mg/ml. Participants are prompted to start out with the 20 mg/ml pods and gradually use pods containing lower nicotine strength when one has been used up.

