**Fig. 4 Fig4:**
[figure not shown]
App section *Training* consisting of (1) 11 therapy modules, and (2) a *Library* featuring a *Toolbox* and meditation audios

As a means of self-monitoring their cessation behavior, users can track the number of smoked combustible cigarettes in the app. Twelve puffs per cigarette are added to their daily EC puffs and depicted accordingly in the app. Additional nuumi app features include a dashboard that participants can use to track their current pod nicotine concentration, number of daily puffs, as well as progress on the behavioral therapy modules, and meditation minutes. Further, as a self-monitoring tool, users are prompted to answer one question concerning their smoking self-efficacy once per week within the app (“How confident are you that you will be completely abstinent from smoking cigarettes in one year from now?” not confident at all—very confident). Daily check-ins take place throughout the first 14 days of the nuumi program. During these check-ins, participants learn more about EC use and receive tips and motivational content to aid their transition from cigarettes to the EC. Users receive daily push notifications containing motivational and informative text messages based on the therapy modules. No substantial revisions to the app are planned during the trial period, and the anticipated app updates are limited to bug fixes.

The nuumi intervention was developed within the framework of Michaelsen and Esch’s Behavior Change Resource Model (BCRM) [28, 59]. The BCRM states that in the development of effective interventions for health behavior change, it is crucial to identify the resources necessary for successful behavior change and to select behavior change techniques (BCTs) most likely to support individuals in reaching their target behavior. Drawing upon a range of theories from social and health psychology, the behavior change process is commonly characterized as involving distinct stages (non-awareness, awareness, contemplation, planning, initiation, continued action, maintenance) that individuals traverse in pursuit of their goal [60]. At each of these stages, individuals require specific resources, defined as factors of an individual that can affect behavior, which can be categorized into three distinct sets, i.e. external, internal reflective, and internal affective resources which are characterized by both changeable and non-changeable factors [28, 59].

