Informed consent	✓					
Intervention:		✓	✓	✓	✓^a^	
Assessments:						
Participants ‘ characteristics						
Age	✓	✓				
Gender	✓	✓				
Height		✓				
Weight		✓	✓	✓	✓	✓
Pregnancy	✓	✓	✓	✓	✓	✓
Primary outcome						
7-day PPA			✓	✓	✓	✓
Secondary outcomes						
CPD	✓	✓	✓	✓	✓	✓
30-days PPA						
Repeated PPA			✓	✓	✓	✓
Continuous PPA			✓	✓	✓	✓
Urges to smoke		✓	✓	✓	✓	✓
Perceived stress		✓	✓	✓	✓	✓
Mindfulness		✓	✓	✓	✓	✓
Smoking self-efficacy		✓	✓	✓	✓	✓
Subjective health		✓	✓	✓	✓	✓
Life satisfaction		✓	✓	✓	✓	✓
Acceptability		✓	✓	✓	✓	✓
Usability		✓	✓	✓	✓	✓
Adherence			✓	✓	✓	✓
Other variables						
Nicotine dependence		✓	✓	✓	✓	✓
Use of alternative tobacco products	✓	✓	✓	✓	✓	✓
Years of smoking	✓	✓				
Motivation to stop smoking	✓					
Quit attempts and method(s)		✓				
Quit date			✓			
Withdrawal symptoms		✓	✓	✓	✓	✓
EC use	✓	✓	✓	✓	✓	✓
NRT use	✓	✓	✓	✓	✓	✓
Participation in another smoking cessation program	✓	✓	✓	✓	✓	✓
Adverse events			✓	✓	✓	✓
EC dependence			✓	✓	✓	✓
Subjective evaluation and side effects of EC			✓	✓	✓	✓
Dropout			✓	✓	✓	✓
Meditation experience & openness towards meditation		✓				

^a^Participants receive unlimited access to the nuumi app; they can use the nuumi EC as long as they have pods (minimum 12 weeks)

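### The protocol does not ensure that the first interview, meant to capture views before the intervention, takes place before participants can use the app or e-cigarette

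*Protocol article*

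**What the plan says.** Under Objectives, the interviews have two purposes. The first is to "explore the perspectives of adults who smoke on quitting using electronic cigarettes and apps before the intervention"; the second is to hear participants' views of the program once they have completed it.

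Participant timeline then fixes the order of events. Interviews are held with a sub-sample of 15 participants around baseline (t0) and week 12 (t3). On recruitment to them: "Interested participants will indicate their willingness to be invited via email at the end of the baseline survey". A separate consent form follows. On timing: "The first interview will be conducted within 2 weeks after t_0_, and the second interview within 2 weeks after t_3". On access: "All participants will receive access to the nuumi intervention directly after t_0_ data collection". The Intervention section names the trigger: "After completion of the baseline survey, participants receive instructions to download the app and will receive a voucher allowing them to order the EC". The device itself comes by post after it has been ordered.

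Later in the Intervention section, the app's onboarding is described: "Daily check-ins take place throughout the first 14 days of the nuumi program". These check-ins teach e-cigarette use and carry motivational content.

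Table 2 in Appendix A ticks the rows for "Acceptability" and for usability at t0 as well as at weeks 4, 8, 12 and 24.

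**The concern.** An interview can be reported as pre-intervention only if it comes before the participant's first contact with the intervention. Here the event that makes someone available for interview 1 (finishing the baseline survey) is also the event that releases the intervention, and the interview may be up to two weeks later.

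Interview 1 asks about attitudes to e-cigarettes and to smartphone apps for quitting. Those views could shift once someone has opened an app that promotes switching to an e-cigarette, or has tried the device. If such interviews are reported as baseline perspectives, a reader cannot separate expectations from early experience. This matters because the article presents the mixed-methods approach as a strength and intends the pilot to inform a randomized trial.

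The Table 2 ticks are a smaller matter in the opposite direction: they place questions about experience of the program at a visit when nobody has yet received it.

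**Working it through.** No stated figure needs reproducing; the check is one of order.

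**Interview 1 against access.** Count days from completion of the baseline survey, which the Recruitment section identifies with t0.

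| Event | Day | Source |
|---|---|---|
| Baseline survey completed; willingness to be interviewed given | 0 | Participant timeline |
| App instructions and voucher released | directly after day 0 | Participant timeline; Intervention |
| Interview consent signed | after day 0, not fixed | Participant timeline |
| Interview 1 | day 0 to 14 | Participant timeline |
| First app login, L | day 0 or later, not fixed | not stated |
| E-cigarette received, E | after ordering and posting, delay not stated | Intervention |

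Let I be the day of interview 1.

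1. Sign-up comes at the end of the survey and a consent form follows, so I cannot precede completion of the survey. Access is released on that completion. The possible lag from access to interview is therefore 0 to 14 days.
2. Interview 1 precedes exposure only if I is earlier than both L and E. The protocol bounds I from above at 14 days, sets no lower bound on L or E beyond day 0, and makes neither wait for the interview.
3. The number of first interviews that follow exposure can therefore be anything from 0 to 15 of 15. The document gives nothing that narrows this range.

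Participant timeline also describes the first interviews as taking place at t0. One might read them as part of t0 data collection, so that access would wait for them. The Intervention section rules this out for practical purposes, because it ties the app instructions and voucher to the survey and not to the interview.

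**Which topics are affected.** Participant timeline lists previous quit attempts, perceived barriers, and perceptions of and attitudes to e-cigarettes and cessation apps. The first two look back. The attitude topics are the ones that early use could alter. Questions on the program's own features and effectiveness are kept for interview 2.

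**Table 2 columns.** The header runs enrollment, t0, t1, t2, t3, t4.
- Acceptability and usability: 5 ticks, t0 to t4.
- Adherence, e-cigarette dependence, and subjective evaluation of the device: 4 ticks, t1 to t4.

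One of five scheduled assessments (t0) falls before access; the other four are well placed. The Secondary outcomes section defines acceptability by satisfaction with the program, its helpfulness and the comprehensibility of its content, and assesses usability of the app with the System Usability Scale. It describes no anticipatory version of these items. Participant timeline answers the outcomes from t3 and t4 data, and the statistical section reports acceptability descriptively. No planned analysis uses a t0 value of either.

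**The case against.** A reader might infer that the first interviews are all contaminated by use of the product. The document does not support that.
- Two weeks is an upper limit, and some interviews may be held within a day or two.
- The e-cigarette has to be ordered and posted, with no delay stated, and participants need not quit at once.
- The 14 days of check-ins are counted from the start of the program, not from t0, so they need not coincide with the interview window.
- Two of the interview topics are largely historical.

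All of this stands, and it limits the point to what the design fails to guarantee. It does not remove the point, because nothing in the text places the interview before exposure.

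A reader might also infer that the baseline ticks would spoil a time trend in acceptability, or that all 70 participants will be asked to rate an app they have not seen. No such trend is planned. The ticks are also weak evidence of what is administered: the same table leaves the row for 30-day abstinence blank although it is a secondary outcome. A misplaced tick is the likelier explanation.

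Finally, re-ordering may come too late. Recruitment began at the end of October 2023 and completion is expected in June 2024. Counting 24 weeks (168 days) back from 30 June 2024 gives 14 January 2024 as the latest baseline, and that participant's interview 1 would be due by 28 January 2024. On these dates many first interviews may already have been held. This is a fair limit on the first remedy, and it is why the fix below has a second part.

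**Conclusion.** The point holds in a limited form. The stated objective and the stated timeline do not fit: interview 1 is meant to precede the intervention but is scheduled after access is released, by up to 14 days. Up to 15 of 15 first interviews could follow first use; the true number may be far smaller and cannot be derived from the document. The consequence is confined to the qualitative pre-intervention objective, chiefly the attitude topics.

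This rests on two readings: that access follows completion of the survey, as the Intervention section says, and that no unstated rule holds access back for interviewees.

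The baseline ticks for acceptability and usability are a scheduling slip that biases no planned result. No primary or secondary quantitative result changes on either count. The interview timing is worth correcting because the remedy is cheap and lets the objective be answered as worded.

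**What to change.** 1. **Interviewees still to be enrolled.** Move the interview invitation from the end of the baseline survey to the consent step. Hold interview 1 before the app instructions and voucher are released, with the baseline survey completed just before release. The survey then remains t0, access still follows it directly, and the follow-up timing is kept. The cost is access a few days later for up to 15 of the 70 participants, and these participants would be interviewed before rather than after their baseline survey.

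2. **Interviews already held, or where step 1 fails.** Record three dates for each interviewee: interview 1, first app login, and receipt of the e-cigarette. Report interviews held after access as early-use rather than pre-intervention, and state how many fall in each group. The cost is some record-keeping and a request to the manufacturer for login and delivery dates.

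3. **Table 2.** Remove the t0 ticks for acceptability and usability so that both rows start at t1, in line with adherence and the device-evaluation rows. This is an edit to the schedule only.

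None of these steps changes an outcome definition, the sample size or a quantitative analysis.

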**Fig. 1 Fig1:**
[figure not shown]
Participant flow and study design

### Intervention

Nuumi is a self-guided digital therapeutic intervention comprising an app-based behavioral therapy and an EC connected to the app via Bluetooth. Initially, participants are asked to use the EC whenever they crave a cigarette, hence replacing cigarettes with the EC. In parallel, participants are prompted to use the app-based behavioral therapy providing information on transitioning to the EC, and smoking cessation. The app also contains information on gradual EC cessation, thus supporting the user in achieving abstinence of both products.

After completion of the baseline survey, participants receive instructions to download the app and will receive a voucher allowing them to order the EC and pods lasting for a minimum of 3 months from the manufacturer’s website at no cost. Participants are also issued a prepaid return label to return unused pods to the manufacturer in case they decide to stop using the EC and/or the program altogether.

Participants are not required to quit smoking immediately after baseline; they are advised to switch from combustible cigarettes to using the EC either by choosing a quit date, or by gradually switching from smoking to using EC over a 2-week period. The EC has been developed and manufactured by the funder of this study. It is a closed system device; i.e. empty pods cannot be refilled by the user and must instead be replaced with prefilled pods obtained through the manufacturer which can only be used after activation via the app.

Participants will receive a kit including the EC, a charger, a power bank, pods, and manuals for the EC and the pods via mail. Each participant will be supplied with an amount of pods equivalent to their respective cigarette consumption at study entry, estimated according to a guideline by the manufacturer. Participants can choose between two kinds of tobacco flavors when ordering the EC. The liquid solution in the pods includes propylene glycol, glycerol, nicotine, and flavoring. The EC is puff activated and the settings cannot be modified by the user. It is powered by a 450 mAh battery.

The participants receive pods in nicotine strength 20 mg/ml to 0 mg/ml, decreasing in steps of two mg/ml. Participants are prompted to start out with the 20 mg/ml pods and gradually use pods containing lower nicotine strength when one has been used up.

The EC is coupled with the nuumi app via Bluetooth, allowing for tracking of patterns of use, e.g. number of daily puffs (see Figure 2). These data are made visible to the user in the app. Two weeks after program start, users are presented a daily puff budget based on their average daily puffs previously recorded and are encouraged not to exceed the number of allotted puffs. Limiting the number of puffs serves the purpose of preventing compensatory puffing [54] when the nicotine concentration in the liquids is reduced. An app feature allows participants to reduce or increase their puff budgets as needed.

**Fig. 2 Fig2:**
[figure not shown]
(1) Bluetooth-enabled nuumi EC, (2) app section *Today* depicting tracking of daily puffs, current nicotine strength, and tracked cigarettes, (3) app section *Progress* showing EC use statistics

To support participants in transitioning to the EC, and to subsequently reach abstinence from the EC, behavioral therapy is provided in the nuumi app which features evidence-based content informed by CBT-based and mindfulness-informed principles. Basis of the behavioral therapy is an initial in-person health promotion and stress management course certified by German statutory health insurance which features information from four core areas, including behavior, exercise, relaxation, and nutrition (BERN, [55, 56]). For the purpose of the present smoking intervention, the course has been digitalized, and its content has been modified to meet the needs of adults who smoke. The content is delivered via educational audio recordings, interactive exercises, and quizzes. The user is prompted to complete a total of 11 modules with each new module made accessible after the previous one has been completed (see Table 1 Appendix A and Fig. 3).

